**Serum brain-derived neurotrophic factor, insulin-like growth factor 1 and inflammatory-marker levels**

Drawing of 8.5 ml venous blood from sedentary patients is performed at t_0_, t_1_ and t_2_. Samples for BDNF, cytokine (insulin-like growth factor-1, tumor necrosis factor-alpha, interleukin-6) and CRP analysis will be taken from a peripheral vein of the arm and collected in serum gel tubes (S-Monovette® Serum, Sarstedt, Nümbrecht, Germany). After complete coagulation at 4 °C, samples will be centrifuged for 10 min. at 1000 g and 4 °C. The serum will be prepared and aliquoted within 24 h after blood drawing. Duplicate samples will be stored at − 80 °C until analyzed when samples of all included participants are collected. Serum levels of BDNF and cytokines are assessed at t_0_, t_1_ and t_2_. BDNF and cytokines will be measured in duplicates in a multiplex analyzer (Bio-Plex 200®, Bio-Rad Laboratories) according to the manufacturer’s instructions. Sera will be thawed, centrifuged for 10 min. at 10,000 g and 4 °C and diluted in sample diluent (1:4). By using the median of the fluorescence intensity and the standard curve, the absolute concentration of BDNF and the cytokines (pg/ml) will be calculated (Bio-Plex Manager 6.1, Bio-Rad Laboratories). For determination of CRP, the blood will be drawn as described above in lithium-heparin tubes (S-Monovette®, lithium-heparin, Sarstedt, Nümbrecht, Germany). It will be centrifuged for 10 min. at 4000 g and 21 °C. Plasma will be aliquoted within 3 h after blood drawing and used fresh. The CRP level will be determined via latex agglutination assay according to the manufacturer’s instructions (C-Reactive Protein Gen.3, cobas®, Roche Diagnostics, Basel, Switzerland). Briefly, plasma will be diluted 1:100 and added on a slide, which is pre-coated with antibodies to monoclonal anti-human CRP and latex reagent. After 2 min incubation, clear agglutination will be observed on the slide and it will be examined turbidimetrically using the analytic system cobas® C702 (Roche Diagnostics). CRP values below 3 mg/l are considered clinically irrelevant and will be adjusted to 0 mg/l.

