• To evaluate the effect of a 6-week whole-body vibration-training vs. placebo on neurotrophin and growth factor expression in adolescent inpatients experiencing a major depressive episode	• In adolescent inpatients experiencing a major depressive episode, the change of brain-derived neurotrophic factor and insulin-like growth factor 1 serum levels from baseline to completion of the 6-week intervention/to 8 weeks’ follow-up differs significantly between the whole-body vibration-training group and the control group (hypothesis C)
• To evaluate the effect of a 6-week whole-body vibration-training vs. placebo on inflammatory-marker expression in adolescent inpatients experiencing a major depressive episode	• In adolescent inpatients experiencing a major depressive episode, the change in tumor necrosis factor-alpha, interleukin-6, C-reactive protein serum levels from baseline to completion of the 6-week intervention/to 8 weeks’ follow-up differs significantly between the whole-body vibration-training group and the control group (hypothesis D)
• To evaluate the effect of a 6-week whole-body vibration-training vs. placebo on self-perceived severity of depression symptoms in adolescent inpatients experiencing a major depressive episode	• In adolescent inpatients experiencing a major depressive episode, the change of Beck’s Depression Inventory-second edition raw-scores from baseline to completion of the 6-week intervention/to 8 weeks’ follow-up/to 20 weeks’ follow up differs significantly between the whole-body vibration-training group and the control group (hypothesis E)
• To evaluate the sustainability of the effect of the 6-week whole-body vibration-training vs. placebo on clinician rated severity of depression symptoms in adolescent inpatients experiencing a major depressive episode	• In adolescent inpatients experiencing a major depressive episode, the change of Children’s Depression Rating Scale-Revised raw-scores from baseline to 8 weeks’ follow-up/to 20 weeks’ follow-up differs significantly between the whole-body vibration-training and the control group (hypothesis F)

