**Placebo control group intervention**

Patients allocated to the PCG-training receive a supervised myofascial release training program. The training sessions consist of seven standardized exercises using a foam roll (Blackroll, Bottighofen, Switzerland): self-massage of the soles of the feet (one leg stand), of the calves (lying in dorsal position), of the hamstrings (lying in dorsal position), of the thighs (manually while lying in dorsal position), of the neck (lying in dorsal position), of the lower and upper back (leaning backwards against a wall in standing position), as well as self-massage of the upper arm and shoulder (leaning sideways against a wall in standing position). Each exercise is repeated 10 times on each side of the body. Between each exercise, participants do low-intensity shoulder and hip mobilization exercises for 2 min. The PCG-intervention was designed to provide an amount of psychosocial stimulation comparable to the WBV-training. All myofascial release exercises are instructed and patients are corrected, if necessary. However, unlike the WBV-training, myofascial release training sessions applied to the PCG hardly induce any muscular effort and cardiovascular stimulation.

Contraindications for participation in a training session in the WBV-training and in the PCG-intervention are acute suicidality, injuries, infections, or fever. To increase adherence to the training, participants are picked up from the ward by study staff. Treatment participation and comments on each session will be recorded.

The WBV-training and PCG-intervention are conducted simultaneously with the patients’ TAU at the Department of Child and Adolescent Psychiatry and Psychotherapy at the University Hospital of Cologne. TAU is carried out by a multidisciplinary team, consisting of psychiatrists, psychotherapists, music therapists, art therapists, pedagogs and social workers. Patients receive psychotherapy in the form of individual sessions one to two times per week. Families are closely involved in the patients’ therapy process. Every 4 weeks, systemic family therapy sessions are conducted. In addition, patients participate in individual and group music-therapy and art-therapy sessions. Counseling by the social services is conducted once or twice during inpatient stay.

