### Statistical analysis

An intention-to-treat analysis will be performed. We will also assess the effect of the complete treatment in a per-protocol analysis. To determine the effects of between-subjects factor “treatment,” within-subjects factor “measurement time point” and their interaction on primary and secondary outcomes, separate 2 × 3 (hypothesis A, E, F)/2 × 2 (hypothesis C, D) mixed ANCOVAs will be conducted. For secondary outcome “HPA axis activity” (hypothesis B) separate 1-factor ANCOVA will be conducted. As covariate, patients’ baseline scores of each specific parameter will be used. A significant main effect of within-subjects factor measurement time point will be further investigated through post hoc pairwise comparisons. Simple effects analyses will be conducted to determine potential group differences at each time point. Due to the exploratory character of the secondary hypotheses, alpha error adjustment will not be applied.

ANCOVA assumptions will be explored. In case of violations of normality assumption, appropriate non-parametric procedures will be used. In case of violations of ANCOVA assumptions of homogeneous variances for between-subjects factor levels and sphericity for variances of differences between categories of within-subjects factor, the F-test will be adjusted. Eta-squared values will be reported as effect size estimates for explained variance, and Cohen’s *d* values will be reported for post hoc pairwise comparisons.

Statistical analysis will be performed by a statistician, blinded to treatment groups. Statistical analyses will be conducted using SPSS 25® (IBM®, Armonk, NY, USA). A result will be considered significant at a *p* value equal to or less than .05.

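### Setting CRP values below 3 mg/l to 0 discards measured variation in the CRP part of hypothesis D and creates artificial jumps at the cut-off

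*Protocol article*

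**What the plan says.** In the protocol article, the serum-marker subsection of Secondary endpoints describes the CRP measurement: "The CRP level will be determined via latex agglutination assay according to the manufacturer’s instructions". It states no detection or quantification limit. It then fixes the recoding: "CRP values below 3 mg/l are considered clinically irrelevant and will be adjusted to 0 mg/l". No such rule is given for TNF-alpha or IL-6.

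Table 1 (Methods/design) sets hypothesis D as a group difference in change: "the change in tumor necrosis factor-alpha, interleukin-6, C-reactive protein serum levels from baseline to completion of the 6-week intervention/to 8 weeks’ follow-up differs significantly".

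Statistical analysis assigns the model ("hypothesis C, D) mixed ANCOVAs will be conducted", in a 2 × 2 layout) and the covariate: "As covariate, patients’ baseline scores of each specific parameter will be used". It adds a fallback: "In case of violations of normality assumption, appropriate non-parametric procedures will be used". The same section calls the secondary hypotheses exploratory and applies no alpha adjustment.

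**The concern.** The hypothesis is about how much CRP changes. The Discussion motivates the marker by linking higher CRP and pro-inflammatory cytokines to lower neurotrophin levels, which is a graded relation. A threshold of clinical relevance does not belong to that question.

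The rule replaces a reported number with 0, so it does three things:
- Movement below 3 mg/l disappears.
- A small movement across 3 mg/l becomes a change of at least 3 mg/l.
- The baseline covariate loses the same information as the outcome.

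If many patients lie below 3 mg/l, a null CRP result would say little about an anti-inflammatory effect, yet could be reported as evidence against one.

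**Working it through.** **1. Arithmetic on the rule (no assumption needed)**

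Let the analysed value be 0 if CRP < 3 mg/l, and CRP as measured otherwise.

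| True values (mg/l) | True change | Analysed values | Analysed change |
|---|---|---|---|
| 3.1 to 2.9 | −0.2 | 3.1 to 0 | −3.1 |
| 2.9 to 3.1 | +0.2 | 0 to 3.1 | +3.1 |
| 2.9 to 0.3 | −2.6 | 0 to 0 | 0 |
| 0.2 to 2.9 | +2.7 | 0 to 0 | 0 |

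In the first two rows the change is overstated by a factor of 3.1 / 0.2 = 15.5. No analysed value can lie strictly between 0 and 3. Every patient below 3 mg/l at both visits contributes a change of exactly 0.

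**2. Inputs for the size of the loss**

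The article gives no power figure for CRP. The only computed figure is the primary-endpoint sample size, which supplies the n used here. A two-sided t test with d = 0.5, alpha .05 and power 80% needs 63.77, so 64 per group. Then (1 − .6²) × 64 = 0.64 × 64 = 40.96, so 41 per group, as stated.

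Assumptions not in the article:
- CRP is lognormal with log-SD 1.1.
- The baseline–post correlation is .6 on the log scale. This value is borrowed from the depression-score planning.
- The median is 0.5 to 5 mg/l.
- The true reduction is 40% or 50%.
- There is one post-baseline visit, which simplifies the planned 2 × 2 model.

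**3. Share of values set to 0**

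The share below the cut-off is Φ((ln 3 − ln m) / 1.1). For m = 0.5 this is Φ(1.792 / 1.1) = Φ(1.63) = 95%. The share at 0 at both visits comes from the simulation without a treatment effect.

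| Median m (mg/l) | Below 3 | Below 3 at both visits |
|---|---|---|
| 0.5 | 95% | 91% |
| 1 | 84% | 76% |
| 2 | 64% | 51% |
| 3 | 50% | 35% |
| 5 | 32% | 19% |

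**4. Power with a true 40% reduction (1,500 simulated trials per row)**

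| Median | Log, as measured | Raw, as measured | Raw, recoded | Rank, as measured | Rank, recoded |
|---|---|---|---|---|---|
| 0.5 | 73% | 47% | 5% | 70% | 8% |
| 1 | 74% | 47% | 24% | 72% | 26% |
| 2 | 72% | 46% | 39% | 68% | 42% |
| 3 | 73% | 46% | 44% | 70% | 50% |
| 5 | 73% | 45% | 46% | 68% | 61% |

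The Monte Carlo standard error is at most √(0.25 / 1,500) = 1.3 points.

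**5. Power with a true 50% reduction**

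Raw-scale ANCOVA on measured values has about 70% power throughout. After recoding it has about 6% at a median of 0.5 mg/l, 25% at 0.8, 43% at 1.2 and 58% at 2. At medians of 3 and 5 it has 70% and 72%, against 72% and 70% unrecoded, so there is no material loss.

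**6. Type I error**

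With no treatment effect, rejection rates in the simulation lay between 2.5% and 5.5%. The recoding does not inflate false positives.

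**The case against.** Several points on the other side stand.

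- **Scope.** A reader might infer that the rule removes most of the signal for hypothesis D. It does not. Hypothesis D also covers TNF-alpha and IL-6, and neither is recoded.
- **Attribution.** It is tempting to compare log-scale power without recoding against raw-scale power with it. That overstates the effect of the rule, because the article plans no log transform. In one run at a median of 1.2 mg/l with a 50% reduction, power was 93% (log), 68% (raw) and 40% (recoded). Of the 53-point gap, 93 − 68 = 25 points come from the scale and 68 − 40 = 28 from the recoding.
- **Missing distribution.** That most adolescent inpatients have CRP below 3 mg/l is plausible, but it is not in the article. Neither are reductions of 40–50%. With a 20% reduction, power would be only about 20% even on unrecoded log CRP.
- **Infection.** A reader might also infer that the values left after recoding mainly reflect intercurrent infection. The only nearby text lists reasons not to attend a training session ("acute suicidality, injuries, infections, or fever"). It says nothing about blood sampling or CRP, so the inference is unsupported.
- **Fallback.** The non-parametric procedure would remove the artificial size of the jump. It cannot separate values tied at 0: rank power still falls from 70% to 8% at a median of 0.5 and from 72% to 26% at 1. This objection therefore stands only in part.
- **Weight.** CRP is one marker in an exploratory secondary hypothesis, and reported values can be re-analysed later if they are kept.

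None of this supplies a reason to overwrite reported values when the question is change in level.

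**Conclusion.** The point holds for the CRP component of hypothesis D. The distortion at 3 mg/l and the loss of all change below it follow from the rule itself. How much power is lost depends on a CRP distribution that the article does not give. Under the stated assumptions the loss on the raw scale is severe at medians around 1 mg/l or lower, modest at 2, and negligible at 3 or above. On ranks some loss remains even there (70% to 50% at a median of 3, for a 40% reduction). The harm is lost power and a distorted effect estimate for one exploratory marker, not false positives. The primary endpoint and the sample size are not affected. Severity: moderate.

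**What to change.** Delete the recoding sentence. Analyse CRP as the assay reports it, preferably log-transformed. State the assay's quantification limit and treat only values below it as left-censored. If the 3 mg/l threshold is of clinical interest, report the share of patients at or above it by group and visit as a separate descriptive result.

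The change needs no new samples or visits. According to Trial status, analysis follows completion of recruitment, so the rule can be changed before the data are analysed. The cost is slightly more analysis work for the censored values. The gain shrinks if the assay's own limit lies near 3 mg/l, so that limit should be checked first.

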**Self-rated severity of adolescent patients’ depression symptoms**

For the self-rating procedure, the German version of the BDI-II [46] is applied. The BDI-II was developed as an indicator of the presence and severity of depression in psychiatric patients from 13 years of age onwards. Twenty-one symptoms are rated by the patient from 0 to 3, with higher scores indicating more severe occurrence of the particular symptom. Accordingly, the sum score ranges from 0 to 63, with higher scores indicating more severe depressive symptomatology. The BDI-II is sensitive for changes in severity of depressive symptomatology. Excellent indices of reliability, as well as good discriminant and convergent validity, have been reported in adolescent psychiatric inpatients [47].
**Sustainability of effects of whole-body vibration strength-training on severity of depression symptoms**

CDRS-R is additionally applied 8 and 20 weeks after completion of the treatment to assess sustainability of potential effects of WBV-training compared to placebo.

The “Balancing Vibrations Study” also comprises magnetic resonance imaging, as well as combined transcranial magnetic stimulation and electroencephalographic recordings. For clarity, the more complex protocols and hypotheses, regarding these neuroimaging/neurophysiological parameters, will be illustrated separately and reported elsewhere.

### Potential confounding factors

Several additional factors, potentially impacting the primary outcome of the study (severity of depression symptoms), are assessed at t_0_. To confirm depression diagnosis and to capture current psychiatric comorbidities, as well as patients’ history of mental disorders, the “Schedule for Affective Disorders and Schizophrenia – Present and Lifetime Version adapted for school-aged children” [48] and the “Diagnostic System for Mental Disorders in Childhood and Adolescence” [49] are applied. For assessment of emotional and/or behavioral problems, the “Child Behavior Checklist/4–18,” as well as the “Youth Self-Report/11–18” of the Achenbach System of Empirically Based Assessment, are used [50]. The patients’ socioeconomic status is assessed with a modified questionnaire developed by Trinkl and colleagues [51].

### Adverse events and compliance assessment

Adverse events and serious adverse events, which are related to the interventions, are assessed by the clinicians. During our pilot study, neither adverse events nor severe adverse events occurred [31]. Compliance to WBV-training and PCG-intervention is protocolled by scientific staff. It was pre-defined that patients need to participate in 20 sessions for complete compliance. This was shown feasible in our pilot study [31].

The Department of Child and Adolescent Psychiatry and Psychotherapy at the University Hospital of Cologne has insurance to cover for non-negligent harm associated with the protocol. This will include cover for additional health care, compensation, or damages. Incidences judged to arise from negligence (including those due to major protocol violations) will not be covered by study insurance policies.

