### Randomization and blinding

Eligible patients are randomized to one of two treatments (see “Groups and treatments” section below). A stratified block randomization with permuted block length is conducted. The stratification factor is patients’ gender (male vs. female). Randomization of treatment groups is implemented based on sealed, opaque envelopes by the Institute of Medical Statistics and Computational Biology of the University of Cologne.

The present study is a double-blinded trial. Prior to participation, patients will be informed that two physical activity interventions (whole-body vibration strength-training/myofascial release training) will be compared regarding their effect on severity of depression symptoms in adolescent inpatients. Accordingly, patients do not know the specific hypotheses of the trial. They will not know if they are allocated to the experimental or to the control group and, therefore, can be considered blinded. Moreover, experimental testing procedures will be carried out by specially trained experimental staff that will also be blinded regarding the allocation of participants to the specific experimental group.

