### Sample size calculation

Sample size calculation was done for the effect of experimental treatment (WBV-training vs. PCG intervention) on the primary endpoint (severity of depression symptoms) measured by CDRS-R raw-scores in an *analysis of covariance* (ANCOVA) model using G*Power 3.1.9.2 software [52]. It was hypothesized that changes in the CDRS-R raw-scores from baseline to completion of the 6-week intervention differ significantly between the WBV-training group and the PCG-training group. As clinically relevant effect size, a medium effect of *d* = .5 was defined. Alpha was set at 5%. Test power (1 − *β*) was set at 80%. Participants’ CDRS-R scores at baseline will be included in the model as covariate. Required sample size in such an ANCOVA model can be calculated as (1 − *ρ*^2^) × *n*, with *ρ* representing the correlation between participants’ baseline and post-treatment outcome scores, and *n* representing the sample size that would have been required if a *t* test of post-treatment outcome scores was applied [53]. Based on the results of our pilot study, we estimated the correlation between patients’ severity of depression symptoms at baseline and at post treatment with *ρ* = .6. Under the presuppositions made, sample size calculation showed that 41 patients in each group (*N* = 82) would be required. We accounted for a 15% dropout rate, leading to a total sample size of *N* = 94 patients.

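### The only stated rule on harms limits the adverse events assessed to those related to the interventions, so events put down to the illness or to usual care could go unrecorded

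*Protocol article*

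**What the plan says.** Under Adverse events and compliance assessment, the article states: "Adverse events and serious adverse events, which are related to the interventions, are assessed by the clinicians". It then cites earlier experience: "During our pilot study, neither adverse events nor severe adverse events occurred".

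Four other places bear on the point:

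- **Groups and treatments, placebo control group intervention.** A rule for both arms on when a session is not to take place: "Contraindications for participation in a training session in the WBV-training and in the PCG-intervention are acute suicidality, injuries, infections, or fever". The same section adds: "Treatment participation and comments on each session will be recorded". Neither sentence is linked to adverse event recording.
- **Randomization and blinding.** Patients are considered blinded, and "experimental testing procedures will be carried out by specially trained experimental staff that will also be blinded". Statistical analysis adds a blinded statistician. The clinicians who assess adverse events are not mentioned in either place.
- **Data collection and timeline.** The two depression scales, CDRS-R and BDI-II, are applied in both arms at t1, t2 and t3.
- **Table 1 and Statistical analysis.** Neither names a safety objective or a comparison of harms between arms.

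**The concern.** In a randomised trial, comparing all events between arms is the main evidence on whether an intervention causes harm. Judging causality case by case is weak where the possible harm resembles the disease. Worsening mood or suicidality in a depressed adolescent inpatient can readily be put down to the illness. If relatedness decides what is assessed, such events can drop out before anyone can see whether they cluster in one arm.

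Safety is part of the case for exercise here. The Background section motivates alternative treatments partly by the side effects of medication and by a raised risk of suicidality in adolescents with two antidepressants. A later statement that no adverse events occurred, like the one quoted for the pilot study, could not separate the absence of events from the absence of events attributed to the training.

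**Working it through.** The article gives no adverse event rate and no figure for harms, so there is nothing to reproduce. The check is of the text, followed by a short illustration on assumed rates.

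**Step 1: what the sentence covers.** The relative clause stands between commas, so two readings are possible.

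- Restrictive: the events assessed are those related to the interventions.
- Non-restrictive: adverse events are assessed, and all of them are, as a matter of fact, related to the interventions. This is implausible for inpatients with major depression who also receive psychotherapy, family therapy and other usual care.

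The restrictive reading is the natural one.

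**Step 2: whether anything else widens the scope.** No section says that events are recorded regardless of cause, or that relatedness is graded after recording. The nearest provision is the per-session record of participation and comments, which is not described as adverse event capture.

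**Step 3: whether relevant events can arise.** Acute suicidality excludes a patient at entry (Table 2) and is also a reason to withhold a session, along with injuries, infections and fever. Suicidality that led to a withheld session would thus be newly arisen since entry. The article provides for the session but not for recording the event as safety data.

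**Step 4: whether attribution could differ by arm.** One arm trains on a vibration plate and the other uses a foam roll. Blinding is stated for patients, testing staff and the statistician, but not for the assessing clinicians. Knowledge of the arm when relatedness is judged is therefore not ruled out.

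**Step 5: illustration.** Take n patients per arm, true event risk p in both arms, and a fraction a of events attributed to the intervention.

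- Expected true events per arm = n × p
- Expected assessed events per arm = n × p × a
- Ratio of assessed events between arms = a₁ / a₂, whatever p is

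The planned total of 94 in Sample size calculation gives n = 94 / 2 = 47. The values p = 20% and the fractions below are assumptions and do not come from the document. True events per arm = 47 × 0.20 = 9.4.

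| Attribution, arm 1 / arm 2 | Assessed, arm 1 | Assessed, arm 2 | Apparent ratio |
|---|---|---|---|
| 50% / 50% | 9.4 × 0.5 = 4.7 | 9.4 × 0.5 = 4.7 | 1 |
| 50% / 10% | 4.7 | 9.4 × 0.1 = 0.9 | 5 |
| 80% / 10% | 9.4 × 0.8 = 7.5 | 0.9 | 8 |

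Equal attribution loses events without distorting the ratio; here half of them go unassessed. Unequal attribution creates a difference where none exists. The table shows the mechanism and estimates nothing about this trial.

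**The case against.** The strongest reply is that one loosely punctuated summary sentence is being made to carry too much. It does not contain the word only. It does not say that the clinicians judge relatedness, or that this judgement comes before recording. A full protocol, not shown, may hold the operational detail. The article plans no comparison of harms, so no planned analysis is damaged.

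Part of this stands. That the clinicians judge relatedness is a reasonable inference, not stated text. The primary endpoint, the power and the efficacy inference are untouched. But the point does not rest on missing detail. The article states a scope, that scope is restricted on its natural reading, and nothing else in it says otherwise.

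Several stronger readings are tempting, and the document does not support them:

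- **The assessors are unblinded ward staff who see the device.** The text says only clinicians. Sessions are run by study staff, and the assessors' blinding is not stated either way.
- **The plan expects suicidality and injuries.** A list of contraindications is a precaution and not a forecast.
- **Events such as self-harm would usually go unrecorded, or capture of unrelated events is nil.** The document gives no basis for a frequency. A withheld session should at least show as non-participation, and worsening depression is measured in both arms by the two scales, whatever its cause.
- **The rule of three gives the size of the problem.** Zero events in 47 patients excludes rates above about 3 / 47 = 6.4%. That bound assumes full capture, so it says nothing about how many events are lost.

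**Conclusion.** The point holds in a limited form. The article's only harms rule restricts assessment to intervention-related events, so events attributed to the illness or to usual care could be missing from the safety data. Any later by-arm report of harms would be open to attribution bias.

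This rests on the restrictive reading of the sentence, on the absence of any wider rule in the article, and, for the bias between arms, on the assessors possibly knowing the arm. The size cannot be computed from the document.

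A reader might infer that a planned safety comparison is invalidated or that the trial's main result is at risk. Neither follows: no such comparison is planned, and the depression outcomes do not pass through this rule. The point merits correction because events not recorded at the time are hard to recover.

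**What to change.** Reword the sentence under Adverse events and compliance assessment so that all adverse events and serious adverse events are recorded in both arms, from randomisation to at least t1, regardless of judged cause. Make relatedness a separate field on the record, ideally completed without knowledge of the arm, and state whether the assessors are blinded. Tabulate all events and related events by arm.

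Sessions withheld for a listed contraindication can prompt an entry, since participation and comments are already recorded for each session. This changes data capture and reporting only; no rule for managing patients is altered.

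Methods/design describes a formal amendment route, and Trial status gives recruitment as ongoing at publication. The amendment should record the date of the change, since capture before and after it will differ. The cost is slightly more documentation by staff, plus one table.
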